
**FIGURE 4 F4:**
[figure not shown]
Five plantar intrinsic foot muscles measured by ultrasound imaging. 1. abductor digiti minimi, 2. Flexor digitorum brevis, 3. Abductor hallucis, 4. Quadratus plantae, and 5. Flexor hallucis brevis. Images purchased via iStock by Getty Images, Calgary, Alberta Canada.

##### Foot structure using navicular drop for foot pronation and hallux valgus angle (first metatarsophalangeal joint)

Navicular drop is a simple and clinically applicable measure of foot pronation requiring only a ruler. It involves measuring the height of the navicular bone from the floor when a participant is seated with the hip and knee at 90° and the foot and ankle positioned in subtalar joint neutral. The participant then moves to bilateral full weight bearing relaxed stance, and the height of the navicular bone is re-measured. The difference is taken between the seated and relaxed stance measures. A normal navicular drop is ≤10 mm while excessive and possibly pathological navicular drop is ≥15 mm (Brody, 1982). We will use these values to indicate improvement in arch height following interventions. Navicular drop has been found a reliable measure for foot pronation by several authors when performed by an experienced clinician (Menz, 1998). Excessive foot pronation is dysfunctional, can lead to several foot disorders and can contribute to falls in older adults (Menz et al., 2006; Hagedorn et al., 2013).

Hallux valgus angle is a simple clinical measure performed with a handheld goniometer with the participant seated with the hip, knee, and ankle joints at 90° and the foot resting on the floor. Hallux valgus is defined as ≥15° of abduction of the hallux from the first metatarsal, and has been further classified into stages of severity (mild 15°–25°, moderate 25°–35°, severe >35°) (Hagedorn et al., 2013). Greater hallux valgus angle has been linked to fall risk by several authors (Menz et al., 2006; Mickle et al., 2009; Koski et al., 1996). Measurement of hallux valgus is typically included in a comprehensive foot exam and was found to have good inter examiner reliability in a population of older adults (kappa values > 0.85, p < 0.01). (Hagedorn et al., 2013). When compared to the gold standard of radiographic measures of hallux valgus, clinical goniometry performed by an experienced clinician was within one°–5.5° (Janssen et al., 2014). Tang et al. conducted a 3 month intervention to reduce hallux valgus angle and found a reduction of 6.5° ± 3.8 resulted in significantly reduced pain and improved walking ability (Tang et al., 2002). Based on Tang et al.‘s work, we will consider a change of ≥7° to be a meaningful improvement. Although IFM function contributes to foot and toe alignment, we have included hallux valgus as an exploratory measure and do not anticipate it will significantly change in an older adult population. This can be likened to the malalignment of an osteoarthritic knee that does not change with exercise intervention alone (Raghava et al., 2001).

A physical therapist researcher with 17 years of clinical experience will perform all foot measures.

Fall Rate will be determined by the number of falls per person in the 12-month study period. Falls will be recorded based on journal entries and will be cross-referenced with subjective reports at 2-week contacts. Researchers and participants will use the operational definition of a fall as an unexpected event in which a person comes to rest on the ground or lower level (Laurence, 2021; Guirguis-Blake et al., 2018).

#### Qualitative and implementation data

At the 16-week measurement point, a semi-structured interview will be conducted with each participant and recorded for later analysis. The purpose of the interview will be to gain understanding of the research activities themselves to inform future studies and also to gain subjective reports of the effects of each intervention. In addition, the journals participants keep regarding adherence to the interventions may inform future research. We will collect participant impressions and level of difficulty regarding performance of their intervention or control activity, comfort of the footwear (for footwear group), pedometer use, adherence to study activities, journal use, and subjective reports on their intervention’s (or control’s) effects on foot awareness (layman’s term for kinesthesia), influence on pre-existing pain or orthopedic conditions, and on balance.

Participants will rate their impressions of intervention or control difficulty on a 5-point Likert scale (e.g., 0 = no difficulty, 1 = mild difficulty, 2 = moderate difficulty, 3 = severe difficulty, 4 = unable to perform). In addition, the semi-structured interview will allow for qualitative data collection regarding participant impressions beyond the Likert scale scores. For example, if a participant has poor adherence to an intervention, follow up questions regarding barriers and facilitators may be valuable in guiding future research or clinical application. Participant impression data may be analyzed to compare participants who drop out of the study *versus* those who complete all interventions and measurement sessions. And finally, adverse events such as pain, injury, or safety concerns will be recorded. An example of a semi-structured interview script can be found in Supplementary Material. The interviews were made as similar as possible for each intervention group.

#### Data collection and management

Participant intake data, foot structure measures, proprioception measures, and Mini-BESTest fall risk measures will be collected on paper intake forms and transferred to a password protected web-based data storage system utilizing spreadsheets. Ultrasound images will be recorded and stored in the ultrasound unit, as well as loaded to a USB thumb drive and transferred to the password protected web-based data storage system. The ultrasound unit, thumb drive, and paper forms will be kept in a locked office with access only to key research personnel. The videos of the Mini-BESTest measures will be uploaded to the password protected web-based data management system and then deleted from the recording device. All data will be de-identified and labeled using an alphanumeric system. Participant contact information and medical history with identifiable information will be kept in a password protected file in the web-based system and in a locked office with access only to key research personnel.

#### Statistical analysis

Fall risk (MiniBESTest scores), muscle CSA of five IFM, Lower Extremity Position Test scores, navicular drop, and hallux valgus angle data will be compared using a *three-group x four-time points* repeated measures analysis of covariance (ANCOVA).

Fall rate will be measured using the number of falls per person in a 12-month period, beginning with the date of the baseline measure. A Cox proportional hazards model will be used to compare falls across groups.

Demographic and potential confounding variables will be collected and included in analyses (e.g., age, sex, height, weight, race, ethnicity, education, pre-trial physical activity (quantified based on the Physical Activity Guidelines for Americans, older adults) (Piercy et al., 2018), pre-trial falls history, comorbidities, medications, self-reported visual impairment, and grip strength).

Implementation variables will be analyzed quantitatively via adherence records and Likert scales, as well as qualitatively via semi-structured interviews.

Our primary analytic approach is an intention to treat analysis. We also will conduct a per protocol analysis for participants who do not complete all study activities (missing data). This may include analysis for mechanisms of missingness: missing completely at random (MCAR), missing at random (MAR) or missing not at random (MNAR). Based on the mechanism of missingness, we may perform a listwise or case deletion or last observation carried forward if appropriate. (Kang, 2013).

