## Abstract

Unintentional falls are the leading cause of injury in adults ≥65 years. While causes of falls are multifactorial, weakness or disuse of the intrinsic foot muscles (IFM) can contribute. The purpose of this randomized controlled trial, using an effectiveness-implementation hybrid design, is to analyze the effects of two IFM strengthening interventions (minimal footwear use or strengthening exercises) on IFM size, proprioception, foot structure, and fall risk in older adults. Adults ages ≥65 years, with fall risk, who can ambulate household distances (with an assistive device as needed), will be invited to participate. Individuals with poor foot sensation, vestibular disorders, lower extremity amputation, lower extremity or lumbar spine injury or surgery in the previous 6 months, impaired cognitive ability to follow verbal and written instructions, and those who have participated in a fall prevention program in the past 6 months will be excluded. Participants will be randomly allocated into three groups: prescribed minimal footwear use, IFM strengthening exercises, or control. Participants will be encouraged to perform their intervention 5 days per week for 16 weeks, and then at least 2 days per week from 17 weeks to 1 year. Participants will be asked to record intervention performance, daily step count, and falls in provided diaries. At baseline, 8 and 16 weeks, and 1 year, participants will undergo measurements of IFM cross-sectional area (CSA, cm^2^) using ultrasound imaging, proprioception, foot structure (navicular drop and hallux valgus angle) and fall risk. Semi-structured interviews will be conducted and recorded to gain participant impressions of the interventions, self-reported effects of the interventions, and impressions of study activities to inform future research and clinical implementation. A three-*group* x four *time point* repeated measures analysis of covariance will be used to assess changes in measurements. Implementation data will be analyzed using both quantitative and qualitative methods. This will be the first study among older adults to assess the effects of IFM strengthening interventions on long-term fall risk and proprioception, and to use ultrasound imaging to assess IFM size changes. These interventions are simple, safe, and affordable and may have a major impact on functional mobility and reduction of falls for older adults.

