### Sample size

An *a priori* power analysis (α = 0.05, power = 80%) was performed for the primary measure of interest: fall risk based on Mini-Balance Evaluation Systems Test (Mini-BESTest) scores. A study by Conradsson, et al. that measured fall risk with the Mini-BESTest following a fall prevention intervention, found a 3-point change in Mini-BESTest scores in the intervention group and a large effect size (Cohen’s d = 0.82) (Conradsson et al., 2015). In addition, Godi et al. performed a reliability, validity, and responsiveness study of the Mini-BESTest and determined the minimal detectable change (MDC) at the 95% confidence interval was 3.5 points (Godi et al., 2013). Based on these previous findings, the power analysis indicated *at least 22 participants per group are needed*. To account for 30% participant attrition, 30 participants per group will be targeted (3 groups, total of 90 participants).

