#### Intervention

There are two interventions and one control activity being compared in this study: prescribed use of minimal footwear, IFM strengthening exercises, and a sham intervention of seated active range of motion of the upper and lower extremities with no foot muscle involvement, accompanied by a brochure with home fall prevention recommendations (control activity). All intervention activities will be prescribed 5 days per week for 16 weeks. After the 16-week intervention period, participants will be encouraged to continue their intervention at least 2 days per week until the end of the 12-month study to maintain gains in muscle strength or endurance (American College of Sports Medicine et al., 2018). At least 2 days of continued training is recommended by the American College of Sports Medicine to maintain muscle strength and endurance (American College of Sports Medicine et al., 2018).

Those in the minimal footwear group will be given a standardized pair of minimal shoes (Figure 3. Xero Aptos, Xero Shoes, Broomfield, CO, United States), and detailed instructions regarding gradual progressive use of the minimal footwear (Supplementary Material). In brief, the instructions include 30 min per day of continuous or non-continuous walking at a self-selected pace (using an assistive device as needed), and also wearing the footwear for progressively longer periods during daily activities.

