#### Outcomes

At baseline, participants will be asked to self-report basic demographics (e.g., age, sex, height, weight, race, ethnicity, highest level of education), as well as history of falls in the past year, current use of an assistive device, level of pre-trial physical activity, and if they feel they spent a lot of their childhood and/or young adulthood barefoot. They will also have dominant hand grip-strength assessed in a seated position using a hand-held dynamometer. (Bohannon, 2019). A detailed medical history, including comorbid conditions and current medications will be collected through a clinical interview process similar to a physical therapy initial evaluation.

Measures of fall risk, proprioception, IFM cross-sectional area (cm^2^), navicular drop, and hallux valgus angle will be taken at baseline and 8-week, 16-week, and 12-month following intervention instruction. These measures will be conducted by two physical therapist researchers with assistance from DPT students. The physical therapist researchers will be blinded to treatment group; however, the DPT students will not be blinded. We have included details of each outcome measure and rationale for selecting the corresponding measurement instruments:

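### If the three-by-four repeated measures ANCOVA uses one pooled within-person error, and correlation with baseline falls by 12 months, 12-month change comparisons get standard errors that are too small and 8-week ones too large; a visit-specific model avoids this

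*Protocol article*

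**What the plan says.** The Statistical analysis section assigns one method to Mini-BESTest, the cross-sectional area of five foot muscles, the Lower Extremity Position Test (LEPT), navicular drop and hallux valgus angle: a "three-group x four-time points" "repeated measures analysis of covariance (ANCOVA"). The Abstract gives its purpose: a "repeated measures analysis of covariance will be used to assess changes in measurements".

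Under Outcomes, these measures "will be taken at baseline and 8-week, 16-week, and 12-month following intervention instruction". The four times therefore include baseline, and the gaps are 8, 8 and about 36 weeks. After week 16 participants are "encouraged to continue their intervention at least 2 days per week", down from 5 days.

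The article does not say whether the model uses one pooled within-person error. It states no covariance structure and no error term for comparisons at a single visit, and it names no visit as primary. It gives no between-visit correlations or visit-specific standard deviations.

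**The concern.** In the usual split-plot form of this analysis, group-by-time is tested against a single subject-by-time mean square. That is valid when the variance of the difference is the same for every pair of visits (sphericity). If follow-up contrasts then borrow the same mean square, every comparison of change from baseline gets the same standard error, whether the follow-up is at 8 or 52 weeks.

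A balance score in older adults would plausibly track baseline less closely after a year than after 8 weeks. Change to 12 months would then be more variable than change to 8 weeks, and one shared standard error would be too small for the first and too large for the second. The 12-month comparison matters because the Abstract presents long-term fall risk as part of what is new in this study. A Greenhouse-Geisser type correction adjusts the omnibus F. It does not change the standard errors of contrasts that use the pooled error.

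**Working it through.** **The plan's own figures.** The Sample size section ("α = 0.05, power = 80"%; "a large effect size (Cohen’s d = 0.82")) concludes that "at least 22 participants per group are needed". A two-sided normal approximation gives 2 × (1.960 + 0.842)² / 0.82² = 23.4, so 24 per group. A one-way three-group F test with f = 0.40 gives 22. The figure is reproduced closely enough and does not bear on this point. It only sets the scale: 30 per group less 30% attrition leaves 21.

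**Inputs.** Visit times are from the Outcomes section. All correlations and standard deviations below are assumptions, because the article gives none. Tests are taken as two-sided at 5%.

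**Formulae.** With equal variances, scaled to 1:
- variance of change used by a pooled error: 2(1 − mean r), where mean r averages the six between-visit correlations;
- true variance of change to visit k: 2(1 − r₀ₖ);
- ratio of pooled to true standard error: R = √(pooled / true);
- actual error rate of a nominal 5% test: 2[1 − Φ(1.96 R)].

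**Case A, high reliability.** Correlations with baseline are 0.85, 0.80 and 0.65; among follow-ups they are 0.88 (8–16), 0.70 (8–52) and 0.72 (16–52). Mean r = 4.60 / 6 = 0.767, so the pooled variance is 0.467. True variances are 0.30, 0.40 and 0.70.

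**Case B, lower reliability.** All Case A correlations are multiplied by 0.75, giving about 0.64, 0.60 and 0.49 with baseline. This is close to the test-retest range of 0.60–0.68 that the article reports for LEPT in healthy older adults. Mean r = 0.575, so the pooled variance is 0.85. True variances are 0.725, 0.80 and 1.025.

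**Case C, equal correlations.** Pooled and true variances coincide.

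**Case D, equal correlation 0.7, SD 1.15 at 8 and 16 weeks and 1 otherwise.** Mean variance is 1.161 and mean covariance 0.808, so the pooled variance of change is 2 × (1.16125 − 0.807625) = 0.707. The true values are 0.7125, 0.7125 and 0.60.

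| Case | R at 8 / 16 / 52 weeks | Actual error rate at 8 / 16 / 52 weeks |
|---|---|---|
| A | 1.25 / 1.08 / 0.82 | 1.5% / 3.4% / 11.0% |
| B | 1.08 / 1.03 / 0.91 | 3.4% / 4.3% / 7.4% |
| C | 1.00 / 1.00 / 1.00 | 5% / 5% / 5% |
| D | 1.00 / 1.00 / 1.09 | 5.1% / 5.1% / 3.3% |

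Simulation of Case A with 21 per arm and no true effect gives about 1.6%, 3.4% and 11% for pooled-error contrasts. Visit-specific errors on the same contrasts give about 5% at every visit. The uncorrected group-by-time F runs at no more than about 7%.

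**Other assumed patterns.** Correlation that decays steadily with time (8-week correlation from 0.95 down to 0.70) gives R at 12 months of 0.74 to 0.82. Decay plus a stable person effect and 10% or 20% measurement error gives 0.84 or 0.89. Shrinking SDs (1, 1, 0.95, 0.9) with equal correlation 0.7 give 0.97 / 0.99 / 1.01, a slight reversal.

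**The case against.** The strongest objection is that the text never specifies the fault. It does not say that the model is univariate or that contrasts share a pooled error, and a group-by-time analysis with visit-specific errors would fit the same words. Covariance structure, sphericity correction and contrast errors are commonly left to a statistical analysis plan, which may exist and is not shown. Their absence is not an error, and this point does not rest on it. The pooled form is an inference from two features: baseline is a level of the time factor, and the remedies offered for incomplete data are case deletion and last observation carried forward, which suit a complete-row analysis more than a likelihood-based mixed model.

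A reader might infer that the 12-month result will be tested at twice the nominal rate. The documents do not support that. Size and direction depend on correlations they do not give, and Cases C and D show no distortion or a reversal at 12 months. Nor does the Case A size carry over to every outcome: LEPT's stated reliability points nearer to Case B.

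Three further limits stand. The distortion concerns comparisons of change. A plain between-arm comparison at one visit, using pooled total variance with equal variances, shows none even when correlation decays. Unequal spacing is not itself the cause; non-sphericity is. And the drop from 5 to at least 2 days per week cannot explain error rates computed under no treatment effect, so it is not used as support here.

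What survives is that change is the stated target of the analysis, that correlation falling by 12 months is plausible, and that the named method in its usual form does not protect against it.

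**Conclusion.** The point holds conditionally. If the named analysis is run with one pooled within-person error, and if correlation with baseline falls over the 36-week gap, the 12-month comparison of change is anti-conservative and the 8-week comparison conservative. Under the two assumed decay patterns the 12-month error rate is about 7.5% to 11% and the 8-week rate about 3.5% to 1.6%. With equal correlations there is no effect. The omnibus test is little affected and can be corrected. This is an inexpensive improvement on a stated method rather than a demonstrated error in the protocol. It is worth making because the 12-month visit carries the long-term claim.

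**What to change.** In the Statistical analysis section, replace the repeated measures ANCOVA with a mixed model for repeated measures: visit as a category, group-by-visit terms, an unstructured within-person covariance and Kenward-Roger degrees of freedom. State that each arm contrast is taken from its own visit-specific estimate and standard error.

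The cost is analysis wording only, with no change to visits or data collection. The statistical price is a few more covariance parameters. With four visits, unstructured covariance has 4 × 5 / 2 = 10 parameters, against 2 for compound symmetry, to be estimated from about 22 evaluable participants per arm (66 in all). Kenward-Roger degrees of freedom are the safeguard at that size.

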#### Randomization

Following screening and enrollment, participants will be allocated to one of three groups using block randomization based on sex (male/female), age (65–84 or ≥85 years) and pre-intervention fall risk based on Mini-BESTest scores (mild risk 28–24, moderate risk 23–18, high risk ≤17). A blinded statistician will create a computerized random number generator, and then create blocks of six with intervention groups randomly assorted in each block (StataSE, Stata Corp, LLC, College Station, TX, United States). Other researchers and participants will not be blinded to intervention group, as this is not possible. However, participants will not be made aware of other intervention groups’ activities.

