**FIGURE 3 F3:**
[figure not shown]
Xero Aptos minimal footwear.

Details and images of the IFM strengthening exercises can be found in Supplementary Material. They include seated lesser toe metatarsophalangeal joint (MTP) flexion/great toe MTP extension, great toe MTP flexion/lesser toe MTP extension, toe abduction, toe adduction, and the short foot exercise (McKeon et al., 2015; Glasoe, 2016; Gooding et al., 2016). These exercises will be prescribed as 3 sets of 10 repetitions for each movement, one time per day.

The control group will perform seated active range of motion activities for the upper and lower extremities, prescribed as 3 sets of 10 for each motion, one time per day. In addition, they will be given a home fall prevention brochure created by the Centers for Disease Control and Prevention (CDC, 2024), and instructed to review it on a weekly basis. These exercise activities will serve as a sham intervention as they do not in any way involve activation of the IFM and are not expected to have any meaningful effects on strength or balance. Details and images of the seated exercises and brochure can be found in Supplementary Material.

After the initial instruction session, instructors will meet with participants again at 1 week and 4 weeks to review intervention performance and answer questions.

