In addition to the above interventions, all participants will be given a pedometer (3D Fit Bud, 3D Active, United Kingdom) and asked to record daily step count in a paper journal. This will allow for comparisons of general physical activity level of each group. Also in the paper journal, participants will be asked to record any falls and the details of the circumstances should a fall occur. To promote intervention adherence and to capture details of falls while fairly recent, participants will be contacted every 2 weeks by researchers from 4 weeks post-intervention instruction to the end of the 12-month participation period. Participants may choose their communication preference for these contacts (email, phone call, or text message). With each contact, five standardized questions will be asked, and a reminder given to not participate in other fall prevention programs while enrolled in the current study:1. Have you experienced any falls (if yes, how many and can you provide details?)2. Are you performing the study activities and do you have any questions or issues?3. Are you using your journal?4. Are you using the pedometer and recording daily step count?5. Have you had any changes in health status?

All participants will be instructed in their intervention activities, pedometer use, and journal use by six trained Doctor of Physical Therapy (DPT) students. Two students will specialize in each group’s activities. Training for each group’s activities will include individual instruction and practice with the primary investigator, who is a physical therapist with 17 years of clinical experience. After instruction, practice, and individual feedback from the primary investigator, each DPT student will individually instruct a physical therapy faculty member unaffiliated with the study, and receive feedback. Written training materials for the DPT students are the same as the instructions that will be given to research participants and can be found in Supplementary Material.

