### Anticipated results

We hypothesize that both IFM strengthening exercises and prescribed minimal footwear use will result in reduced fall risk exceeding the established MDC (3.5 points) or MCID (2 points), improved proprioception, and increased IFM size (CSA), and will result in no change in foot structure measures. Those participants performing IFM strengthening exercises will likely have greater changes in muscle size than those using minimal footwear due to the intentional recruitment of the IFM. However, the changes in fall risk and proprioception will likely not differ significantly between minimal footwear use and IFM strengthening exercise groups. We hypothesize no changes will occur with fall risk, proprioception, IFM size, and foot structure in the control group.

It is unknown how our cohort of older adults will receive the IFM strengthening exercises or minimal footwear, but based on limited evidence in nations outside the United States, some older adults can successfully perform these interventions. Our study will be conducted in a region with cold weather, which could limit adherence to minimal footwear use. We plan to encourage participants to use footwear in large indoor spaces such as shopping malls. Severe foot and toe stiffness could make performance of the IFM strengthening exercises difficult for some individuals. We do not anticipate any limitations for the control (sham intervention) group.

Several factors have been included in the study design in an effort to keep participants engaged in the study for 12 months. We have seven in-person meetings planned for measurement and intervention instruction and review. In addition, each participant will have two specific Doctor of Physical Therapy students assigned to them for intervention instruction, intervention review, scheduling, and bi-monthly contacts. This personal connection may keep participants adherent and engaged in study activities.

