### Potential limitations and solutions

We acknowledge a few limitations of this study, with possible solutions or mitigations.

Falls are multifactorial and caused by internal and external factors. The specific inclusion and exclusion criteria of this study attempts to minimize many internal confounding factors including poor foot sensation, vestibular disorders, cognitive impairments, amputations, and recent injury or surgery.

The participants will be asked to self-report falls, details of falls, intervention adherence, and step count in a paper journal. We recognize that self-reported data can be inaccurate or unreliable; however, we have mitigated this with a plan to contact participants every 2 weeks as a reminder and a supplemental way to collect this same data.

Our decision to collect foot measures using only the right foot is one based on time and resources for both researchers and participants. We recognize people can have asymmetry in the feet in terms of foot dominance, structure or pathology. Having only right foot measures limits the generalizability of our results.

The study will be conducted in an area of the United States with extremely cold winter weather. This may limit some participants’ ability to engage in the prescribed walking/wearing schedule of the minimal footwear. We will recommend people walk in minimal footwear in safe indoor spaces such as grocery stores or shopping malls, but accessibility to those spaces may be limited based on socioeconomic status. In addition, it is possible that participants wearing minimal footwear will be more unstable initially compared to their customary footwear. The walking/wearing schedule takes this into account with a very conservative increase in wear time to allow for the musculoskeletal and neuromuscular systems to gradually adapt to the footwear’s wider, thinner design.

This study addresses the very substantial clinical and community health issue of falls in older adults. The overall design and attention to detail will produce high quality research that may provide researchers, clinicians, policymakers, and older adults themselves with simple solutions to this highly relevant problem.

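### The 12-month fall window opens at the baseline measure, before allocation, while visits and fall contacts run from instruction and the two-weekly fall check starts only at week 4 (minor)

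*Protocol article*

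**What the plan says.** All references are to the protocol article.

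- **Fall clock.** Statistical analysis: "Fall rate will be measured using the number of falls per person in a 12-month period, beginning with the date of the baseline measure", and "A Cox proportional hazards model will be used to compare falls across groups". The Participants section likewise runs participation for 12 months from the baseline measures.
- **Visits.** Outcomes: the measures "will be taken at baseline and 8-week, 16-week, and 12-month following intervention instruction".
- **Fall contacts.** Intervention: "participants will be contacted every 2 weeks by researchers from 4 weeks post-intervention instruction to the end of the 12-month participation period". The first of the five standard questions asks about falls.
- **Review meetings.** Intervention: "instructors will meet with participants again at 1 week and 4 weeks to review intervention performance and answer questions".
- **Order of events.** Randomization is stratified by sex, age and "pre-intervention fall risk based on Mini-BESTest scores". The Intervention section has journal use taught together with the allocated activity. Anticipated results: "We have seven in-person meetings planned for measurement and intervention instruction and review".
- **Source of fall data.** The fall-rate paragraph at the end of Outcomes takes falls from the journal and checks them against the two-weekly reports. Potential limitations and solutions accepts that self-report can be wrong and gives those contacts as the mitigation.
- **Early period.** The same section says "it is possible that participants wearing minimal footwear will be more unstable initially compared to their customary footwear", and then says that the slow increase in wear time is meant to allow for this.

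**The concern.** There are two linked problems.

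First, the trial has two time origins. Falls and participation are counted from baseline, visits and contacts from instruction. Allocation cannot happen until the baseline Mini-BESTest is scored, so the fall window opens before anyone has been randomized. A fall recorded in that interval would enter the outcome although no allocated activity could have caused or prevented it. At the other end, the 12-month fall window and stated participation finish before the 12-month visit, by exactly the length of the gap.

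Second, the check that the article relies on to make self-reported falls credible is not scheduled to begin until 4 weeks after instruction. Those weeks are also the ones in which the authors think footwear users might be less steady. At stake is the reading of early falls as a safety matter and, to a lesser degree, the 12-month fall comparison.

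**Working it through.** **1. Is instruction separate from baseline?** The article's own figure is seven meetings for measurement, instruction and review. Measurement visits: baseline, week 8, week 16, month 12 = 4. Instruction = 1. Review meetings at weeks 1 and 4 = 2. Total 4 + 1 + 2 = 7, which reproduces the stated figure. Merging baseline and instruction would give 6. So baseline comes before allocation (certain, from the stratification), and instruction appears to be a later session (inferred from the count).

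**2. Time from the start of the clock to the first standardized fall question.** With a gap of g weeks between baseline and instruction, this is g + 4 weeks, or (g + 4)/52 of the window. The gap is not stated; 0 to 4 weeks is an assumption.

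| g (weeks) | g + 4 | (g + 4)/52 | g/52 |
|---|---|---|---|
| 0 | 4 | 7.7% | 0% |
| 1 | 5 | 9.6% | 1.9% |
| 2 | 6 | 11.5% | 3.8% |
| 4 | 8 | 15.4% | 7.7% |

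**3. Dilution from falls recorded before treatment.** Assume constant fall rates, full capture, no treatment effect during the g weeks and a rate ratio r afterwards. Over 52 weeks the observed ratio is [g + r(52 − g)]/52, so

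observed ratio − 1 = (r − 1) × (1 − g/52).

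The distance from 1 shrinks by the fraction g/52, that is by 1.9%, 3.8% or 7.7% for gaps of 1, 2 or 4 weeks. This is a rate-ratio approximation to the Cox result. If the Cox model uses time to first fall, which the article does not say, a fall in the gap would also use up that participant's only event.

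**4. Expected falls in weeks 0-4 after instruction.** Assume 0.5 to 1.0 falls per person-year (not in the article) and the 30 per group that it targets: 30 × 0.5 × 4/52 = 1.15 and 30 × 1.0 × 4/52 = 2.31. That is roughly one to two falls per arm.

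**5. Effect of weaker early capture.** Let the footwear arm's fall rate in weeks 0-4 be k times that of the comparator, with equal rates afterwards. Let a share c of early falls be captured in every arm, and all later falls. With g = 0, the observed 12-month rate ratio is (4kc + 48)/(4c + 48).

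| k | c = 1 | c = 0.8 | c = 0.6 |
|---|---|---|---|
| 1 | 1 | 1 | 1 |
| 2 | 56/52 = 1.077 | 54.4/51.2 = 1.0625 | 52.8/50.4 = 1.048 |
| 3 | 60/52 = 1.154 | 57.6/51.2 = 1.125 | 55.2/50.4 = 1.095 |

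With no early excess (k = 1), equal under-capture leaves the ratio at 1. With an early excess, the ratio is understated, but only modestly over 12 months. The values of k and c are illustrations, not figures from the article.

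**The case against.** A reader might infer more than the documents support, in three ways.

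*That untreated, unrecorded time pulls the comparison toward no difference.* It does not. In a Cox model, time in which no event is recorded adds no term to the partial likelihood, and a similar lead-in shifts all arms alike. A rate ratio is also unchanged if every arm carries the same proportion of such time. Only falls that are recorded before allocation dilute a ratio. This objection stands, and the point is confined to those falls.

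*That early falls go unobserved.* They do not. The journal is in use from instruction, participants see their instructors at weeks 1 and 4, and the standard fall question has no look-back limit, so the first contact can cover the whole period. The documented loss is that one recall interval may be 4 weeks instead of 2. What instructors ask at the review meetings may also be detail left to a fuller document.

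*That the plan is biased in favour of minimal footwear.* The capture schedule is the same in all arms, so this needs an early excess of falls in the footwear arm. The article raises initial instability only as a possibility and pairs it with a deliberately slow build-up of wear time.

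It is also fair to say that the gap may be only a day or two, and that the study overview figure, which might settle it, is not available here. None of this removes the stated rule that the fall window begins at baseline, its conflict with the origin used for visits and contacts, or the late start of the named safeguard.

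**Conclusion.** The point holds as a minor one. The stated fall window opens before allocation and, by the meeting count, probably before instruction; it also ends before the 12-month visit. Any fall recorded before allocation would dilute the comparison, by about 2% to 8% of the distance from 1 for an assumed gap of 1 to 4 weeks and by almost nothing if the gap is a few days.

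Separately, the cross-check on self-reported falls is absent from the stated schedule for the first 4 weeks after instruction, 7.7% of a year. If the footwear arm has an early excess, it would be modestly understated: 1.077 read as 1.048 under a doubling with 60% capture. Otherwise no bias between arms is expected. The more practical loss is a less secure reading of early falls, where only one or two per arm are expected at the assumed rates. The primary measure, the Mini-BESTest, is unaffected.

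**What to change.** - In Statistical analysis, start the fall clock at randomization, with instruction on the same day or as close to it as possible. Randomization is the safer origin: a later instruction date could drop people who were randomized but never instructed, which would sit badly with the intention-to-treat approach.
- Use that one origin for falls, visits and end of follow-up in Participants, Intervention, Outcomes and Statistical analysis, so that the fall window and the 12-month visit end together. Record falls between baseline and randomization as history, not as outcome events.
- In Intervention, state that the existing standardized fall question is asked at the existing week-1 and week-4 meetings.
- Optional: one remote contact at week 2, and a summary of falls in weeks 0-4 by arm.

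The cost is a change of wording and one question added to two meetings that already take place. The optional contact would add one short message or call per participant. No extra visits are needed.
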